#### 12.1.3 Exploratory outcome measure

- Change in JAK2-V617F, CALR 5bp insertion (exon 9), or CALR 52bp deletion (exon 9) allele burden between weeks 12, 24 and baseline.
- Proportion of patients showing a decrease in requirement for cytoreduction at 24 weeks compared to baseline
- Proportion of patients showing a decrease in the peripheral blood JAK2-V617F, CALR 5bp insertion (exon 9), or CALR 52bp deletion (exon 9) mutant allele burden of  $\geq 50\%$  at 36 and 48 weeks compared to baseline

- Duration of reduction in the peripheral blood JAK2-V617F, CALR 5bp insertion (exon 9), or CALR 52bp deletion (exon 9) mutant allele burden, defined as time from first observed reduction of  $\geq 50\%$  until reduction from baseline becomes  $< 25\%$  or patient death.
- The expression (RNAseq), DNA-protein interaction (CHIP-Seq) and methylation studies focused on oestrogen receptor signalling in haematopoietic progenitors will be performed in the lab of [name] at the University of Cambridge following the collection of peripheral blood (baseline and 24 weeks, plus 36 weeks and 48 weeks if patients continue treatment beyond 24 weeks as applicable) and bone marrow aspirate samples (24 weeks only).

## 12.2 Analysis of Outcome Measures

### 12.2.1 Primary outcome measure

Analysis of the primary outcome will be completed on an intention to treat basis. The proportion of patients who have achieved the primary outcome of a reduction in allele burden of  $\geq 50\%$  will be presented. Given 3 or more patients have achieved this level of reduction in allele burden the treatment will be deemed to show evidence of activity and will warrant further investigation. Patients who die or are lost to follow up prior to the primary end point of 24 weeks will be classed as non-responders.

### 12.2.2 Secondary outcome measures

All secondary outcomes will be analysed in a descriptive manner on an intention to treat basis with no formal hypothesis testing taking place.

- The reduction in the allele burden of  $\geq 50\%$  at 12 weeks will also be obtained following analysis of peripheral blood at University of Cambridge. Counts and percentages of patients who have achieved each level of reduction at 12 weeks will be presented. Patients who die or are lost to follow up prior to 12 weeks will be classed as non-responders.
- The total number of grade 3 and 4 adverse events reported will be presented as well as the number of patients who have experienced one or more of these events.
- The total number of thrombotic events (of all grades) will be reported as well as the number of patients who have experienced one or more of these events.
- Haematological response at weeks 12 and 24 will be tabulated and compared using a  $\chi^2$  test or Fisher's exact test if the first is not considered appropriate.
- Proportion of patients in each response category at 24 weeks of treatment will be presented as the number and percentage of patients in each category.
- Proportion of patients showing an improvement in response category at 24 weeks will be presented as the number and percentage of patients who have shown an improvement (or maintained a CR).

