## 7. TREATMENT DETAILS

### 7.1 Trial Treatment

Tamoxifen is considered an investigational medicinal product (IMP) for the purposes of the trial from the point of dispensing.

Sites are to use tamoxifen from standard hospital stock. No free or discounted product is offered as part of the trial.

Any brand of tamoxifen may be used provided it is in tablet form and administered orally.

Medication labels in English will be provided in the Pharmacy File. These must be added at the point of dispensing and the local information and patient trial number added.

Patients should be given enough tamoxifen to last until their next scheduled visit but the schedule for prescribing is at local site discretion (e.g. can be prescribed 4 weekly initially, rather than 2 weekly).

Patients will receive 20mg once daily. Patients should start trial treatment following registration but this must be within 6 weeks of the assessment of allele burden and continue daily for 24 weeks. At this point, further treatment may be prescribed if the patient is receiving benefit (at the discretion of the treating Investigator).

As guidance, treatment continuation will be encouraged but not mandated for patients who do not experience persistent side effects greater than grade 1 or thrombotic events of any grade and that fulfil one or more of the following criteria at 24 weeks:

- $\geq 25\%$  reduction in allele burden compared to baseline
- Improvement of haematological response compared to baseline without changes in cytoreductive therapy dose according to 2009 ELN criteria for ET/PV patients and to IWG-MRT response criteria for MF patients
- A decrease in requirement for cytoreduction without deterioration of haematological response compared to baseline according to 2009 ELN criteria for ET/PV patients and to IWG-MRT response criteria for MF patients

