### 8.1.3 Reporting period

Details of all AEs (except those listed above) will be documented and reported from the date of commencement of protocol defined treatment until 28 days after the administration of the last treatment. SAEs that are judged to be at least possibly related to tamoxifen must still be reported in an expedited manner irrespective of how long after IMP administration the reaction occurred. Special attention should be paid to women who develop endometrial problems.

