#### 12.1.2 Secondary outcome measures

- Proportion of patients with a reduction in the peripheral blood JAK2-V617F, CALR 5bp insertion (exon 9), or CALR 52bp deletion (exon 9) mutant allele burden of  $\geq 50\%$  at 12 weeks
- Toxicity measured as the number of grade 3 and 4 adverse events reported.
- The number of thrombotic events of any grade reported and validated.
- Haematological response, assessed at weeks 12 and 24, for patients who enter the study in response (CR or PR). Haematological response is defined according to 2009 ELN criteria for ET/PV patients and no evidence of disease progression for MF patients according to IWG-MRT response criteria (for criteria see Appendices 5 & 6).
- Proportion of patients in each response category according to IWG-MRT response criteria for MF patients and 2013 ELN response criteria for ET/PV patients at 24 weeks of treatment.
- Proportion of patients showing an improvement in response category at 24 weeks compared to baseline according to 2009 ELN criteria for ET/PV patients [1] and according to IWG-MRT response criteria [2] for MF patients. Patients who are in a higher category at week 24 compared to baseline will be classed a success. Patients who enter the trial in CR and who maintain a CR will also be classed as a success in this outcome.

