### 12.4 Planned Interim Analysis

Accumulating data will be analysed and presented on a regular basis (6 monthly) to an independent TSC for monitoring of safety and futility. Analysis will also be performed and presented to the TSC if 7 or more patients out of the first 21 patients registered are deemed to not have tolerated treatment. A patient is classed as not being able to tolerate treatment if they discontinue treatment due to:

- Unacceptable toxicity, defined as:
  - Grade 3-4 adverse event considered related to tamoxifen
  - Persisting grade 1-2 adverse events considered related to tamoxifen lasting more than 14 days and that do not resolve within 4 weeks of reducing tamoxifen to 10 mg od
- Thrombotic event of any grade

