### 13.4 Trial Steering Committee

Data analyses will be supplied in confidence to an independent TSC which will be asked to give advice on whether the accumulated data from the trial, together with the results from other relevant research, justifies the continuing recruitment of further patients. During the recruitment phase of the trial the TSC is scheduled to meet 6 monthly. Additional meetings may be called if recruitment is much faster than anticipated and the TSC may, at their discretion, request to meet more frequently or continue to meet following completion of recruitment. An emergency meeting may also be convened if a safety issue is identified. The TSC would also be convened to monitor the safety of the trial in mind of the efficacy if 7 out of the first 21 patients registered to the trial do not tolerate treatment. See section 12.4.

The TSC will report directly to the Trial Management Group (TMG) who will convey the findings to the Sponsor, MHRA, REC or funder if applicable. The TSC may consider recommending the discontinuation of the trial if the recruitment rate or data quality are unacceptable or if any issues are identified which may compromise patient safety.

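### The 7-of-21 tolerability trigger counts registered patients, but only a patient who has started tamoxifen can count towards the 7

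*Combined protocol and SAP*

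**What the plan says.** **Analysis set.** Section 12.2.2 opens with "All secondary outcomes will be analysed in a descriptive manner on an intention to treat basis with no formal hypothesis testing taking place". Grade 3-4 toxicity and thrombosis are both secondary outcomes. I found no definition of intention to treat, no treated or safety set, and no rule for replacing registered patients who never start.

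**Safety outputs.** Section 12.1.2 defines the toxicity outcome as "Toxicity measured as the number of grade 3 and 4 adverse events reported". Section 12.2.2 then plans counts: "The total number of grade 3 and 4 adverse events reported will be presented as well as the number of patients" with at least one such event, and "The total number of thrombotic events (of all grades) will be reported as well as the number of patients" with at least one. No percentage is requested for either. In the same section, percentages are requested for the 12-week allele-burden outcome and for both response-category outcomes.

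**Trigger.** Section 12.4 adds an analysis for the TSC "if 7 or more patients out of the first 21 patients registered are deemed to not have tolerated treatment". Section 13.4 repeats the rule: the TSC would be convened "if 7 out of the first 21 patients registered to the trial do not tolerate treatment". Section 12.4 classes a patient as intolerant only on discontinuing treatment because of unacceptable toxicity (as defined there) or a thrombotic event.

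**Order of events.** Section 7.1: "Patients should start trial treatment following registration", within 6 weeks of the allele-burden assessment. Section 8.1.3 has adverse events recorded "from the date of commencement of protocol defined treatment until 28 days after the administration of the last treatment".

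**The concern.** Registration and first dose are separate steps, so a patient can be registered and never start. Such a patient cannot discontinue treatment, and so cannot be classed as intolerant, but still takes up one of the first 21 places. The numerator of the trigger therefore comes from treated patients and the denominator from registered patients. Any mismatch makes the rule harder to reach, which is the wrong direction for a safety check.

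The rule matters because section 1.2.2 justifies the design partly by criteria for evaluating toxicity, on the ground that tamoxifen is new in this disease and in combination with cytoreductive agents. The 7-of-21 rule is the only numerical criterion of that kind in the plan.

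A related gap is that the safety summaries in 12.2.2 have no treated denominator to be read against.

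**Working it through.** **The plan's own design figure.** Section 12.6 gives 42 patients, success at 3 or more responders, rates of 2% and 10%, one-sided alpha 0.1 and power 80%. Exact binomial: P(X ≥ 3 | 42, 0.02) = 0.0515 and P(X ≥ 3 | 42, 0.10) = 0.805. The smallest sample size meeting both limits is 42, so the figure reproduces. Nothing below alters it.

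**Inputs for the trigger.** The threshold of 7 and the denominator of 21 registered come from 12.4 and 13.4. Two further inputs are not in the documents and are assumed: k, the number of the first 21 who never start (0 to 3), and p, the true intolerance rate among treated patients (20% to 50%).

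**Step 1: observed rate needed to fire.** With k non-starters, 7 intolerant patients must come from 21 − k treated:

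- k = 0: 7/21 = 33.3%
- k = 1: 7/20 = 35.0%
- k = 2: 7/19 = 36.8%
- k = 3: 7/18 = 38.9%

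**Step 2: chance of firing.** P(X ≥ 7) with X binomial on 21 − k patients at rate p:

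| True rate p (assumed) | k = 0 | k = 1 | k = 2 | k = 3 |
|---|---|---|---|---|
| 20% | 0.1085 | 0.0867 | 0.0676 | 0.0513 |
| 30% | 0.4495 | 0.3920 | 0.3345 | 0.2783 |
| 33.3% | 0.5801 | 0.5194 | 0.4557 | 0.3903 |
| 40% | 0.7998 | 0.7500 | 0.6919 | 0.6257 |
| 50% | 0.9608 | 0.9423 | 0.9165 | 0.8811 |

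The k = 0 column is also what the rule delivers if it is counted on 21 treated patients.

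**Step 3: the outputs in 12.2.2.** Totals of events, and numbers of patients with at least one event, do not change when untreated patients join the set. A percentage would change. With k now counted among all 42, a rate on 42 registered equals the rate on treated patients multiplied by (42 − k)/42. That is 0.976 for k = 1 and 0.952 for k = 2, or about 1/42 = 2.4% of its value per non-starter. For example, 10 affected patients are 10/42 = 23.8% of registered patients, against 10/40 = 25.0% of treated patients when two never start.

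**The case against.** A reader might infer that untreated patients dilute every safety rate in the trial. The documents do not support that. The toxicity and thrombosis outcomes are defined and presented as counts, and the authors ask for percentages elsewhere in the same section when they want them. This part of the objection stands in full: dilution would arise only if percentages on the registered set were added.

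The size of the trigger effect is also open to challenge. The documents give no number of non-starters, and the gap is short. Section 6 requires allele burden to be confirmed before registration, the schedule of events shows dosing from registration, and the drug is a tablet from hospital stock. None or one non-starter among the 21 is quite plausible, and with none the effect is nil. The protocol also states no target intolerance rate and no operating characteristics for the rule, so the 33.3% and 40% scenarios are illustrations. At low true rates, a smaller chance of firing might even be seen as fewer false alarms. All this limits the size of the effect. It does not remove the mismatch, which never makes the trigger easier to reach.

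Finally, the trigger is not a stopping boundary. It prompts an extra analysis, while the TSC already receives accumulating data every 6 months (12.4), reviews all serious adverse events (8.2.5) and can meet urgently on a safety issue (13.4). Six intolerant patients among 19 treated would still come before it. This also stands, and is why the point is minor.

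**Conclusion.** The point holds for the trigger. As worded in 12.4 and 13.4, the rule loses sensitivity with each of the first 21 registered patients who never starts. With 1, 2 or 3 such patients (assumed), the chance of firing falls from 0.580 to 0.519, 0.456 or 0.390 at an assumed true intolerance of 33.3%, and from 0.800 to 0.750, 0.692 or 0.626 at an assumed 40%. The calculation treats patients as independent with a common intolerance rate. The practical consequence is modest, since a missed trigger means one prompted review fewer alongside routine oversight.

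The safety outputs in 12.2.2 are not biased as planned. What they lack is a stated treated denominator, which would matter once percentages were reported.

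**What to change.** - **12.4 and 13.4:** count the trigger on the first 21 patients who receive at least one dose of tamoxifen. The threshold of 7 and the definition of intolerance stay as they are.
- **12.2.2:** summarise toxicity and thrombosis in patients who received at least one dose, and state that number as the denominator. This would also settle how to treat a thrombosis between registration and first dose, since the thromboembolic Event Form in 9.1 has no stated start date.
- **Activity outcomes:** keep intention to treat, under which the plan already classes deaths and losses to follow-up as non-responders.

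The cost is a wording change in three sections. The sample size and the 3-responder rule are unaffected. The one downside is that the 21st evaluable patient may be reached slightly later. If everyone starts, the safety counts are identical. The trigger is then also unchanged, except that the first 21 to start may not be exactly the first 21 registered.

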### 12.2.3 Exploratory outcome measure

All exploratory outcomes will be analysed in a descriptive manner on an intention to treat basis with no formal hypothesis testing taking place.

- Change in allele burden at 12 and 24 weeks compared to baseline will be obtained following analysis of peripheral blood at University of Cambridge and will be presented as the median change from baseline at each time point with the interquartile ranges.
- Proportion of patients showing a decrease in requirement for cytoreduction therapy at 24 weeks compared to baseline will be presented as the number and percentage of patients who have a decrease in treatment dose. Patients who die or are lost to follow up prior to week 24 will be classed as non-responders.
- Proportion of patients showing a decrease in allele burden of  $\geq 50\%$  at 36 and 48 weeks compared to baseline will also be obtained following analysis of peripheral blood at University of Cambridge. Counts and percentages of patients who have achieved the reduction at 36 and 48 weeks will be presented. This will only be presented for patients who remain on treatment post week 24 and are assessed at week 36 and week 48, respectively.
- 
- Duration of reduction in the peripheral blood JAK2-V617F, CALR 5bp insertion (exon 9), or CALR 52bp deletion (exon 9) mutant allele burden, defined as time between visits from first

observed reduction of  $\geq 50\%$  until the visit at which reduction from baseline becomes  $< 25\%$  or the last visit before the patient dies, will be tabulated.

- Expression (RNAseq), DNA-protein interaction (ChIPSeq) and methylation studies will be analysed and presented by the University of Cambridge.

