## 3. TRIAL DESIGN

This is a single arm, open label, multicentre, phase II trial of tamoxifen in patients with MPNs.

The aim of the study is to evaluate the activity of tamoxifen in terms of reducing allele burden and the safety of giving tamoxifen in this group of patients. A single stage A'herns design has been chosen to give evidence of activity for the treatment.

All patients will receive a minimum of 24 weeks of treatment with tamoxifen at 20mg od. Patients will be seen at weeks 4, 12, 18 and 24. Mutant allele burden of JAK2-V617F, CALR 5bp insertion (exon 9) and CALR 52bp deletion (exon 9) will be assessed at baseline. Allele burden will be reassessed at 12 weeks and 24 weeks for the mutation(s) identified at baseline. Patients may continue treatment

beyond 24 weeks at the discretion of the treating Investigator. If patients do continue treatment they should be followed up a minimum of 12 weekly and their allele burden reassessed at 36 weeks and 48 weeks as applicable. All patients will be followed up until 28 days after the last dose of tamoxifen treatment.

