### 4.2 Exclusion Criteria

- Leukaemic transformation ( $>20\%$  blasts in blood, marrow or extramedullary site).
- Accelerated phase of disease as indicated by  $\geq 10\%$  blasts in the peripheral blood
- Treatment of ET, PV or MF with Interferon alpha or other investigational agents for their MPN within 6 months prior to trial entry. JAK inhibitors, such as ruxolitinib, are allowed if taken continuously for  $\geq 6$  months prior to registration (dose changes during that period will be allowed)
- Any of the following previous thrombotic events at any time:
  - Portal or other splanchnic venous thrombosis
  - Vascular access complication
  - Ischemia cerebrovascular
  - Stroke
  - Transient Ischaemic attack
  - Superficial thrombophlebitis
  - Venous Thromboembolic events including pulmonary embolism (PE) and deep vein thrombosis (DVT)
  - Peripheral vascular ischemia
  - Visceral arterial ischemia
  - Acute coronary syndrome
  - Myocardial infarction

- Previous malignancy within 5 years with the exception of adequately treated cervical carcinoma in situ or localized non-melanoma skin cancer
- Previous endometrial cancer, hyperplasia or polyps
- Prior treatment with hematopoietic stem cell transplantation
- Patients who do not carry JAK-2V617F, CALR 5bp insertion (exon 9) or CALR 52bp deletion (exon 9) mutations, or whose allele burden is <20% at study entry (**assessed via central review**)
- Female patients receiving hormone replacement therapy
- Hypertriglyceridemia > grade 1
- Any serious underlying medical condition (at the judgment of the Investigator), which could impair the ability of the patient to participate in the trial (e.g. liver disease, active autoimmune disease, uncontrolled diabetes, uncontrolled infection (HIV, Hepatitis B and C), known genetic defect (apart from MPN) relating to venous thromboembolic events, or psychiatric disorder precluding understanding of trial information)
- Known hypersensitivity to tamoxifen or hypersensitivity to any other component of tamoxifen
- Concomitant drugs contraindicated for use with the trial drug according to the Summary of Product Characteristics (Appendix 8)
- Known planned scheduled elective surgery during study with the exception of dental and low risk eye surgery (e.g. cataracts)

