### 7.6 Supportive Treatment

Patients should continue to receive cytoreductive therapy for their MPN such as hydroxycarbamide or anagrelide, in addition to other supportive treatment such as venesection or aspirin as applicable. However, patients must not receive any treatments listed in section 7.7.

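### The cytoreduction outcome counts only dose decreases, so it cannot separate a net fall in requirement from balanced titration or a net rise

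*Combined protocol and SAP*

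**What the plan says.** Section 12.1.3 defines the exploratory outcome as "Proportion of patients showing a decrease in requirement for cytoreduction at 24 weeks compared to baseline", and the Synopsis and Section 2.2.1 define it in the same way. Section 12.2.3 says that the result "will be presented as the number and percentage of patients who have a decrease in treatment dose", and adds: "Patients who die or are lost to follow up prior to week 24 will be classed as non-responders". It sets no minimum size of decrease. It plans no count of increased or unchanged doses, no summary of the size of change, and no rule for patients who switch or combine agents.

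Three features of the design bear on this:

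- **No comparator.** Section 3: "This is a single arm, open label, multicentre, phase II trial of tamoxifen in patients with MPNs".
- **Background therapy continues and its dose is not fixed.** Section 4.1 requires cytoreductive therapy at entry. Section 7.6 says "Patients should continue to receive cytoreductive therapy for their MPN such as hydroxycarbamide or anagrelide". Section 4.1 bars new agents in the 6 months before registration but sets no stable-dose rule. For JAK inhibitors in that period, Section 4.2 states that "dose changes during that period will be allowed".
- **A related criterion elsewhere is stricter.** The continuation guidance in Section 7.1 lists "A decrease in requirement for cytoreduction without deterioration of haematological response compared to baseline". The outcome in Section 12.2.3 does not carry that condition on haematological response.

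On the status of the analysis, Section 12.2.3 states: "All exploratory outcomes will be analysed in a descriptive manner on an intention to treat basis with no formal hypothesis testing taking place".

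**The concern.** The outcome asks whether patients need less cytoreduction after 24 weeks of tamoxifen. Every patient enters on such therapy, so each dose can fall, stay the same or rise. The planned summary keeps only the falls. A patient whose dose was raised is scored like one whose dose did not change.

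A randomised comparison would show the background rate of dose reduction in the control arm. Here there is none, and the obvious internal reference, the number of patients whose dose went up, is not reported. A descriptive outcome has only its table to convey the result, and this table leaves out the direction of net change. The plan does treat a decrease as favourable, since deaths and losses are called non-responders for this outcome. A one-sided percentage could therefore be taken as a fall in requirement when the cohort as a whole shows none.

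Other outcomes in the same plan are reported more fully. Section 12.2.3 gives change in allele burden as a median with interquartile range, which shows direction and size. Section 12.2.2 gives response at 24 weeks by category.

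**Working it through.** **The plan's own figure.** The documents give no figure for this outcome. The sample size of 42 belongs to the primary outcome (Section 12.6: 2% against 10%, one-sided alpha 0.1, power 80%, 3 or more responders). It reproduces by exact binomial calculation: with n = 42, P(3 or more) is 0.0515 at 2% and 0.805 at 10%, and 42 is the smallest n that meets both limits. It is used below only as the denominator.

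**Step 1: what the planned count leaves out.** Let d be the number with a decrease, i the number with an increase, and n = 42.

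- Planned summary: d/n.
- Net difference: (d - i)/n.
- Standard error for paired data: sqrt[(d + i) - (d - i)²/n]/n.
- 95% CI: net difference ± 1.96 × standard error.

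Take d = 8, so the planned summary is 8/42 = 19.0%.

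| Increases i | Planned report | Net difference | Standard error | 95% CI |
|---|---|---|---|---|
| 0 | 19.0% | 8/42 = +19.0% | sqrt(8 - 64/42)/42 = 0.0606 | 7.2% to 30.9% |
| 8 | 19.0% | 0/42 = 0.0% | sqrt(16)/42 = 0.0952 | -18.7% to +18.7% |
| 16 | 19.0% | -8/42 = -19.0% | sqrt(24 - 64/42)/42 = 0.1129 | -41.2% to +3.1% |

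The planned report is the same in all three rows. This follows from the definition and needs no assumption about how often doses change.

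**Step 2: how many decreases could arise with no net change.** This step does need an assumption, because the documents give no titration rate. Suppose a proportion q of patients is on a lower dose at week 24 than at baseline, and the same proportion q is on a higher one. The expected net change in the cohort is zero, and the expected number counted as decreased is 42q.

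| Assumed q | Expected number counted as decreased | Chance of at least one, 1 - (1 - q)^42 |
|---|---|---|
| 5% | 2.1 | 88.4% |
| 10% | 4.2 | 98.8% |
| 15% | 6.3 | 99.9% |
| 20% | 8.4 | over 99.9% |
| 30% | 12.6 | over 99.9% |

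Over this range, about 2 to 13 of 42 patients would be reported as having a reduced requirement although increases and decreases balance.

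**Step 3: the condition on haematological response.** Section 7.1 accepts a decrease as a reason to encourage continued treatment only if haematological response has not deteriorated. Section 12.2.3 counts any decrease. A dose cut made for low counts or intolerance, or followed by loss of response, would therefore count as a success. Reporting increases as well would not remove this; the decreases also need to be split by response.

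**The case against.** The strongest reply is that very little rests on this outcome. It is one of five exploratory outcomes, with no test, no threshold and no place in the decision rule of 3 or more allele-burden responders. That stands, and it sets the weight of the point.

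The titration rates are assumed. Entry is limited to patients with stable, well-controlled disease, and for PV and ET blood counts must have stayed within limits for 3 months, so dose changes may be uncommon. That also stands. The 2 to 13 of 42 is an illustration; the identity in Step 1 is not affected.

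A net difference does not supply a control arm either. It has a true null of zero only if increases and decreases would balance without tamoxifen, and nothing in the documents establishes that. Drift in the disease and prescribing habits remain mixed with any drug effect. The net difference shows direction, but it does not support attribution.

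A reader might go further and infer that ordinary titration is bound to be presented as a tamoxifen benefit. The documents do not support this. Section 12.2.3 attributes nothing to tamoxifen, and the count need not be positive: it is zero if doses move only upward, and at a 5% downward rate the chance of no decrease in 42 patients is about 12%. The comparison is also week 24 against baseline, so a dose that falls and then returns is not counted.

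**Conclusion.** The point holds as a limitation of one exploratory summary. A two-way quantity is reported in one direction only, and in this single-arm design the reported percentage cannot distinguish a net fall in cytoreduction requirement from no net change or a net rise. With 8 decreases among 42 patients, the same 19% covers net differences from +19% to -19% in the examples shown, and that needs no assumption. The figure of about 2 to 13 patients counted as decreased with zero net change rests on assumed equal rates of 5% to 30% in each direction.

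It would be wrong to infer that the trial's conclusion on activity is at risk, since no decision depends on this outcome. This is a minor improvement, worth making because it is cheap.

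**What to change.** In Sections 12.1.3 and 12.2.3:

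- Classify each patient at week 24 against baseline as decreased, unchanged, increased or missing. Missing covers deaths and losses to follow-up, who remain non-responders as now planned.
- Show switches of agent in a separate row, so that a change of drug is not forced into increased or decreased.
- Report the net difference (decreased minus increased) over all patients, with a 95% confidence interval for paired data.
- Give the median and interquartile range of the percentage dose change for patients who stay on the same single agent.
- Cross-tabulate decreases by whether haematological response was maintained, using the criteria already named in Section 7.1.
- Keep the analysis descriptive, and state that without a control arm a net change cannot be attributed to tamoxifen alone.

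The cost is some wording and one extra table. No new visit or sample is needed. Section 9.1 lists a Concomitant Medication Form completed continuously. It does not say that dose is recorded, but the outcome as planned already needs it, so the trials office should confirm that the form captures it. The drawback for the sponsor is that the reported benefit may look smaller.
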